### Analytic plan

3.3.

Analysis will be conducted after completion of the 3-year time frame for all participants according to the pre-specified plan and using intention-to-treat protocol. Mortality will be analyzed as a screen failure but is expected to be rare and balanced by arm. For Aim 1, we will fit a generalized linear model (GLM) for the binomial family with a logit link, robust standard errors, and fixed effects for treatment arm and clinic to compare colonoscopy outreach to no outreach, sequential outreach to no outreach, and sequential outreach to colonoscopy outreach, separately for the primary outcome. [42] We will perform a similar analysis for the detection of adenomas, sessile serrated polyps or advanced adenomas and a zero-inflated Poisson regression model with robust standard errors for the proportion of time covered by screening tests (number of days screened). [43] We will also include socioeconomic and clinical variables in a secondary multivariable model, including age, sex, race, insurance type, income (zip code level), and prior CRC screening, along with interaction terms with the clinician directed EHR nudge assignment. This will allow us to evaluate the effect of patient outreach in the context of visit-based nudges. We will perform a subgroup analysis of Black patients for each of the primary comparisons and conduct additional subgroup analyses for non-rare subgroups in an exploratory fashion, including the same socioeconomic and clinical variables described above for all.

For Aim 2 (visit-based nudge comparison), we will again fit a generalized linear model (GLM) for the binomial family with a logit link, robust standard errors, fixed effect for clinic, and study arm at stage 1 (no outreach, colonoscopy outreach, sequential choice outreach) and stage 2 (nudge, no nudge) to compare visit-based nudges to usual care for the primary outcome. Individuals who attended at least 1 PCP visit will be included in this analysis. As a sensitivity analysis we may consider the potential interaction between the terms for the arm at stage 1 and at stage 2. This will allow us to evaluate the effect of visit-based nudges in the context of colonoscopy and sequential choice outreach. We will perform a similar analysis for the detection of adenomas, sessile serrated polyps or advanced adenomas and a zero-inflated Poisson regression model with robust standard errors for the proportion of time screened (days). We will also include socioeconomic and clinical variables in an exploratory multivariable model, including age, sex, race, insurance type, income (zip code level), and prior CRC screening, along with interaction terms with the patient outreach choice assignment. We will also conduct a sensitivity analysis to examine whether those that showed up for a visit in each arm are similar to those that were originally randomized to that nudge arm, and conduct a reweighted analysis in order to be representative of those originally randomized. We will perform a subgroup analysis of Black patients for each of the primary comparisons and conduct additional subgroup analyses for non-rare subgroups in an exploratory fashion, including the same socioeconomic and clinical variables described above for all.

To evaluate the performance of the 3-year mortality index algorithm, we will perform a 3-year descriptive retrospective evaluation of CRC ordering rates, CRC screening completion rates, number of emergency department visits, number of hospitalizations, and mortality among all patients excluded from participation by the mortality index algorithm.

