## Introduction

1.

Colorectal cancer (CRC) is the second leading cause of cancer death in the United States (US). Routine screening has reduced the burden of disease, but national screening still falls below goals, with rates at approximately 67 %. [1–5] There are also persistent racial, ethnic and socioeconomic disparities in outcomes, particularly among Black patients. [6,7] Multi-level approaches that decrease clinician and patient barriers are important for durably increasing screening rates, including both direct population-based outreach along with clinician recommendations during visits. [8] However, these approach have not been adopted widely and have been difficult to sustain over time.

New insights from behavioral science have helped recognize that humans use systematic shortcuts in thinking that thwart long-term health goals. [9–11] For example, present-time bias reduces the motivation to engage in behaviors whose outcomes are not immediate; status quo bias makes past choices the more likely future choices; and choice overload paralyzes decision making, even when stakes are high. [12–14] However, there is evidence that we can harness these same biases to encourage healthy behaviors. [15,16] Reminders can overcome present-time bias; shifting from opt-in to opt-out framing can increase participating in cancer screening; and both can simplify decisions and prevent overload. [17–21]

Colonoscopy and fecal immunochemical testing (FIT) are evidence-based and top-tier tests for CRC screening. [4,22] FIT achieves a higher response rate in a single outreach, but it requires annual adherence. [23,24] Colonoscopy is more sensitive for identifying polyps and cancer, but the procedure is costly and burdensome for patients. [8] There is evidence that offering a choice of testing can boost screening rates, but there is the potential for choice overload. [25,26] Sequential choice that offers colonoscopy first, then FIT to those who decline or defer has the potential to simplify choice, and it is recommended by clinical guidelines, but there is limited evidence to support this approach. [27–29]

This trial evaluates a multi-level screening intervention that combines direct outreach and nudges in the electronic health record (EHR) during visits to durably increase screening rates. We incorporate behavioral principles such as opt-out framing and reminders while evaluating the comparative effectiveness of sequential choice compared to colonoscopy only.

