### Interventions

2.4.

All patients randomized to an outreach arm (arms 2 and 3) receive centralized direct outreach to complete colonoscopy. Regional physician leads sign bulk order colonoscopy for eligible patients, while the primary care provider (PCP) is listed as the authorizing provider. Patients receive outreach via the electronic patient portal (if active status) or mailed letter informing them their PCP has ordered the procedure, including the colonoscopy order (mailed only) and providing the phone number for direct access to colonoscopy. Outreach is conducted in batches of approximately 4000 patients every 2 months to minimize the burden on clinical services. Additionally, at the time of initial outreach, all patients in arms 2 and 3 receive a text message from the PCP or practice indicating that their primary care provider has already ordered a colonoscopy, with scheduling information. Text messaging via the Way to Health platform is bidirectional, offering automated replies to common colonoscopy related questions. If text messaging is not available, the patient receives similar messaging using Automated Voice Recording (AVR).

Patients who are not up-to-date on screened based on EHR data (Epic Health Maintenance), do not schedule their colonoscopy within 2 months from initial outreach, and have not been ordered for multitarget stool DNA (MT-sDNA) receive an additional mailed and text message reminder. Those in arm 2 (colonoscopy only) receive a mailed reminder about colonoscopy scheduling. In arm 3 (sequential choice), patients receive a mailed FIT kit with instructions, a pre-paid return envelope and a letter describing the stool test as an annual alternative to colonoscopy. The FIT order is signed in bulk by the regional physician lead, with results going back to the PCP as the authorizing provider.

Patients in arms 2 and 3 who have still not completed FIT, or either scheduled or completed colonoscopy at 4 months, receive a final text message reflecting their study arm assignment recommendation. This centralized, direct patient outreach is repeated annually for patients who are not up-to-date on CRC screening, in the same 4 batches of the prior study year.

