### Outcomes

3.1.

The primary trial outcome is patient completion of CRC screening at 3 years, which can be satisfied by any one of the following: colonoscopy completion at any time, negative FIT completed 2 times, or positive FIT followed by diagnostic colonoscopy within 1 year. The secondary outcomes include CRC screening completion at 3 years by any modality (to include anything satisfying the primary outcome, or completion of sigmoidoscopy, CT colonography, or MT-sDNA); the proportion of time that the patient is adherent to CRC screening process completion (during the 3 years of the study from the date of randomization); and the detection of adenomas, sessile serrated polyps, and advanced neoplasia (adenomas greater than 1 cm, or with high-grade dysplasia or villous histology, or invasive CRC). We will also evaluate the choice of screening test (colonoscopy, FIT, or other modalities) and potential screening harms such as colonoscopy perforation or post-polypectomy bleeding.

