### Sample size and power

3.2.

For the patient-directed analysis (Aim 1), after completion of the 3-year time frame for all participants, we will compare CRC screening completion for participants in each of the outreach arms, colonoscopy outreach (arm 2) and sequential outreach (arm 3), separately to the no outreach arm (arm 1); and we will also compare completion between colonoscopy (arm 2) and sequential outreach (arm 3) using intention-to-treat protocol. This includes all patients randomized, such that no evidence of completed CRC screening will be recorded as incomplete and not “missing” regardless of follow-up in the health system. Mortality will be analyzed as a screen failure but is expected to be rare and balanced by study arm. We estimate base CRC screening completion rate of 27 % in arm 1 (no outreach), which is based on estimates of response from a prior study. [29] With 20,000 patients randomly allocated in a 1:2:2 ratio, we will have 85 % power to detect a 3-percentage point increase in response rate of arms 2 and 3 relative to arm 1, and comparing arm 3 to arm 2, accounting for a total of three pairwise comparisons with a two-sided Type 1 error rate of 0.017 (Bonferroni correction of 0.05/3 = 0.017); we will also have 96 % power to detect a 3-percentage point increase in response rate for arm 3 compared to arm 2 (assuming 30 % completion in arm 2 and 33 % completion in arm 3).

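### The zero-inflated Poisson model named for proportion of time screened splits the effect in two and, as specified, names no single effect over all randomised patients

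*Protocol article*

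**What the plan says.** The Outcomes section (3.1) lists as a secondary outcome "the proportion of time that the patient is adherent to CRC screening process completion", measured over the 3 years from randomisation. Every patient therefore has a value between 0 and 1, or between 0 and about 1095 days.

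The Sample size and power section (3.2) sets the population for Aim 1: "This includes all patients randomized, such that no evidence of completed CRC screening will be recorded as incomplete". The Analytic plan (3.3) repeats that the analysis is by intention to treat.

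For this outcome the Analytic plan names, for Aim 1, a "zero-inflated Poisson regression model with robust standard errors for the proportion of time covered by screening tests (number of days screened", and for Aim 2 a "zero-inflated Poisson regression model with robust standard errors for the proportion of time screened (days". It does not say whether arm enters the zero part, which coefficient is the treatment effect, or whether a mean over all randomised patients will be reported.

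Three other statements bear on the direction of the effect:
- The Introduction says that "FIT achieves a higher response rate in a single outreach, but it requires annual adherence".
- Under Interventions (2.4), the mailed FIT goes to arm 3 only, with "a letter describing the stool test as an annual alternative to colonoscopy".
- The primary outcome is met by "colonoscopy completion at any time, negative FIT completed 2 times, or positive FIT followed by diagnostic colonoscopy within 1 year".

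**The concern.** Days covered is a share of a fixed window, not a count of events. A zero-inflated Poisson model assumes that some zeros come from the Poisson part. At hundreds of days per screened patient that part yields practically none, so the model separates into two pieces: the odds of any cover, and the mean days among patients with some cover.

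The second piece compares patients selected by being screened, which is what the outreach is meant to change. In arm 3 the mailed FIT may bring in patients who would otherwise have had no cover, and whose cover is shorter than that from a colonoscopy. They raise total time covered but can lower the average among the screened. Robust standard errors correct the variance; they do not change what is being compared.

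This secondary outcome weighs durable cover from colonoscopy against annual FIT. If the count ratio were read as the effect, the arm 3 v arm 2 comparison could show no difference, or favour arm 2, while mean cover per randomised patient is higher in arm 3.

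**Working it through.** **Plan's own figures.** The article gives no planning figure for this outcome. Its primary-outcome powers reproduce: 85.1% for 27% v 30% (4000 v 8000) and 95.5% for 30% v 33% (8000 v 8000), two-sided alpha 0.017, against the stated 85% and 96%. The 30% v 33% rates anchor the illustration.

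**Step 1. The model becomes two-part.** The Poisson probability of zero at a mean of 600 days is exp(-600), effectively 0. Hence mean days per randomised patient = P(any cover) × mean days among the covered, and the count ratio is the ratio of the second factor alone.

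**Step 2. Assumptions not in the documents.** One FIT gives 365 days and two give 730. A colonoscopy covers from its date to day 1095. Arm 2 has 30% colonoscopy. Arm 3 has 30% colonoscopy, 3% with two FITs and 6% with one FIT. Single-FIT users do not meet the primary outcome, so primary completion is 30% v 33%.

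**Step 3. Expected values.** The added users contribute 0.03 × 730 + 0.06 × 365 = 43.8 days per randomised patient, or 43.8/1095 = 0.04 of the window. The share with any cover is 0.30 v 0.39.

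| Mean colonoscopy cover (days) | Mean days among screened, arm 2 v 3 | Count ratio | Mean days per randomised patient, arm 2 v 3 | Ratio |
|---|---|---|---|---|
| 550 | 550 v 535 | 0.97 | 165.0 v 208.8 | 1.27 |
| 700 | 700 v 651 | 0.93 | 210.0 v 253.8 | 1.21 |
| 800 | 800 v 728 | 0.91 | 240.0 v 283.8 | 1.18 |
| 900 | 900 v 805 | 0.89 | 270.0 v 313.8 | 1.16 |

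For example, at 800 days: 0.30 × 800 + 43.8 = 283.8, and 283.8/0.39 = 728. The count ratio falls below 1 whenever mean colonoscopy cover exceeds the added users' average of 43.8/0.09 = 487 days.

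**Step 4. Sensitivity to the mix.**
- If the only added users are the 3% with two FITs, the gain is 0.03 × 730 = 21.9 days and the all-randomised ratio is 1.13 to 1.08. The count ratio runs from 1.03 (550 days) to 0.98 (900 days).
- Suppose FIT partly replaces colonoscopy, with FIT users covered 500 days: arm 2 has 27% colonoscopy and 3% FIT, arm 3 has 24% and 14%. At 800 days per colonoscopy, 0.27 × 800 + 0.03 × 500 = 231 and 0.24 × 800 + 0.14 × 500 = 262 (ratio 1.13). Among the screened, 231/0.30 = 770 and 262/0.38 = 689 (ratio 0.90). At 550 days per colonoscopy the latter are 163.5/0.30 = 545 and 202/0.38 = 532 (ratio 0.98).

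**Step 5. Simulation at the actual arm sizes** (7735 and 7732), with the Step 2 mix and colonoscopy dates uniform over days 30 to 899. In 500 trials the average count ratio was 0.948 and the average all-randomised difference was +44 days. Both were significant at the 1.96 threshold, in opposite directions, in 99.6% of trials.

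**Step 6. What the fitted model returns.** In one simulated trial the raw means over all randomised were 188.7 v 242.7 days (difference 54.0, SE 5.3), and the fitted count ratio was 0.941 (635 v 598 days).
- Arm in both parts: P(any cover) × mean days gives 188.7 v 242.7, the raw arm means.
- Arm in the count part only: the model uses one pooled P(any cover) of 0.352 and gives 223.2 v 210.1, so the overall effect is reversed.

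**The case against.** The strongest reply is that a reader might infer that the planned model gives no randomised answer at all, and that this is wrong. It is wrong. The zero part compares all randomised patients, and with arm in both parts the marginal means return the raw arm means (Step 6). The article nowhere says that the count ratio will be reported as the effect or that arm is left out of the zero part. A full analysis plan, not shown here, may settle this. That part of the reply stands.

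A reader might also infer that arm 2 will be favoured. The documents do not support that either. They give no test mix and no days of cover per test, and Step 4 shows ratios near or slightly above 1 under other plausible mixes. The 99.6% figure belongs to one assumed mix.

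Two further points also hold. Days and proportion differ only by a constant when the window is fixed, and robust standard errors deal with the excess variance. The argument is also weaker for Aim 2: the two nudge groups (2a + 3a and 2b + 3b) contain the same outreach arms in nearly equal numbers, 7732 v 7735 by the counts under Randomization (2.3).

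The reply does not remove the point. The article commits to this model for a bounded share of time, and the model's natural output is two effects, one of them conditional on being screened. No statement in the article ties them back to the intention-to-treat population.

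**Conclusion.** The concern holds in a limited form. The named model suits this outcome poorly and, as specified, identifies no single effect over all randomised patients. For arm 3 v arm 2 its count ratio can be near or below 1 while mean time covered per randomised patient is higher in arm 3: 0.97 to 0.89 against 1.27 to 1.16 in the main illustration, and 1.03 to 0.98 against 1.13 to 1.08 if all added users complete two FITs. Leaving arm out of the zero part could distort the overall effect as well. These sizes rest on the assumed cover durations and test mix. The all-randomised contrast can still be recovered from the planned model if arm is in both parts and marginal means are reported. This is a secondary outcome, so the primary analysis and its power are unaffected. It should be changed before the analysis.

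**What to change.** For Aim 1, define the effect as the difference between arms in the mean proportion of the 3-year window covered (also given in days) over all randomised patients, zeros included. Estimate it by linear or fractional-logit regression with robust standard errors and fixed effects for arm and clinic. Keeping the zero-inflated model is acceptable if arm enters both parts and the reported effect is the contrast of marginal means. Present the share with any cover and the mean days among the covered as description only.

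For Aim 2, use the same effect measure within its stated population of patients with at least one PCP visit. Changing the model does not turn that subset into all randomised patients.

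The cost is a few sentences in the analysis plan and a simpler model. No new data are needed, and the article schedules the analysis only after all participants have completed 3 years.

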Patients randomized to a visit-based nudge arm (2B or 3B) who attend a visit with their PCP additionally receive a visit-based, clinician-directed nudge and a follow-up text 3 days post-visit. The nudges include an EHR static highlighted notification (Epic storyboard banner)(Fig. 2) notifying clinical staff (medical assistants, PCPs, and nursing staff) that a colonoscopy and/or FIT order has been placed on their behalf and encouraging discussion around completion. Patients receive a follow-up text message 3 days after the visit reminding them to follow through on active CRC screening orders (colonoscopy, FIT, or both).

Participants randomized to arm 1 (usual care) do not receive any direct outreach or visit-based nudges from this trial. Fig. 1 summarizes the trial design.

As per usual care across the health system, endoscopy reports and follow-up recommendations are provided to patients by the performing gastroenterologist, and patients completing FIT are also be notified of their results. If a FIT positive patient does not schedule diagnostic colonoscopy follow-up within two months of their result and has not received standard follow-up outreach from the practice, the research team sends a note in the EHR to population health coordinators who will provide additional support.

We will obtain baseline data from the EHR on demographics, prior CRC screening, co-morbidities, and mortality risk from automated data extraction and free text searches, as needed. We will use chart review to track outcomes of colonoscopies that are performed with polypectomy, so that we can categorize the finding. Study data are being collected and managed using REDCap electronic data capture tools hosted at the University of Pennsylvania. [37,38]

Changes in Health Maintenance (HM) status are assessed via daily Clarity query to identify documentation of screening results and determine continued outreach. All HM status changes and results (internal or external) picked up by this query are chart-reviewed and only counted toward an outcome if documentation is present in the patient chart.

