For the visit-based analysis (Aim 2), we will compare the primary outcome of CRC screening completion among patients in the direct outreach arms (who have at least 1 visit with the PCP) between the usual care arm (arms 2 A + 3 A) and the visit-based nudge arm (Arms 2B + 3B) that receives clinician directed nudges during the visit and follow-up text messages. Patients in the direct outreach arms (arms 2 and 3) will be randomized in a 1:1 ratio to either receive (A) usual care/no visit-based nudge, or (B) visit-based nudge plus follow-up text. Based on retrospective analysis in this population, we estimate approximately 80 % of patients in each arm will have at least 1 visit during the course of the trial, which translates to 12,800 patients in arms 2 and 3 that will be included in the visit-based analysis (about 6400 in each arm). As this group receives direct outreach, we anticipate a 31.5 % (the average of the estimated completion rate among all patients between Arm 2 and Arm 3) response across the intervention arms for usual care (no visit-based nudges). We will have 80 % power to detect a 2.3 percentage point increase in response rates of arm B relative to arm A.

For our pre-specified subgroup analysis, we estimate 25 % of the study population (5000 patients) will be Black with a baseline completion rate of 23 %, so we will have 80 % power to detect a 5.5 percentage point increase in arms 2 and 3 compared to arm 1, and 80 % power to detect a 4.7 percentage point increase in arm 3 compared to arm 2 (assuming 28.5 % completion in arm 2). For the visit-based nudge comparison and a baseline completion rate of 30.9 % (the average of the estimated completion rate among Black patients between Arm 2 and Arm 3), we estimate that least 80 % of black patients will have at least one visit during the trial (3200 patients), and that we will have 80 % power to detect a 4.7 percentage point increase in arm B compared to arm A (estimate 4000 in arms 2 and 3 in the visit-based analysis).

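### The Aim 2 analysis set includes patients who met the primary outcome before their first PCP visit, which dilutes the nudge comparison, and it does not match the plan's general intention-to-treat statement

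*Protocol article*

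**What the plan says.** The Analytic plan (3.3) opens by committing the analysis to proceed "according to the pre-specified plan and using intention-to-treat protocol". Section 3.2 spells out, in its Aim 1 paragraph, that this means everyone randomised, with no evidence of screening counted as not completed.

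For Aim 2 the set is narrower. Section 3.2 compares groups A and B of the direct outreach arms among those "who have at least 1 visit with the PCP", and section 3.3 repeats: "Individuals who attended at least 1 PCP visit will be included in this analysis". The visit may fall anywhere in follow-up. The sample size assumes that "approximately 80 % of patients in each arm will have at least 1 visit during the course of the trial", giving 12,800 patients or about 6400 per group, and states 80% power for a 2.3-point gain over 31.5%.

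Under Interventions (2.4), a patient in 2B or 3B receives the nudge on attending a PCP visit, and a text three days later "reminding them to follow through on active CRC screening orders". Under Outcomes (3.1), a colonoscopy counts whenever it occurs in the 3 years.

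Section 3.3 also plans a check that attenders resemble those randomised to the same nudge arm, and an analysis reweighted to represent the randomised patients.

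**The concern.** Central outreach goes directly to every patient in arms 2 and 3 and does not depend on a visit. Some will therefore complete colonoscopy first and see their PCP later. The planned set counts them because they had a visit, although by then their primary outcome was settled. They are successes in A and in B alike, and the nudge had nothing left to change.

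Such patients shrink the observed difference between A and B and add variance without information. What is at stake is the sensitivity of the main Aim 2 test, which is sized at about 80% power with no margin to spare. There is also a labelling problem. A reader who takes the general intention-to-treat sentence at face value would expect all 15,467 patients randomised to A or B, and the described Aim 2 comparison does not use them all.

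**Working it through.** **Inputs.** From section 3.2: 6400 per group, 31.5% in A, a gain of 2.3 points, 80% attendance. From section 2.3: A = 3865 + 3867 = 7732 and B = 3870 + 3865 = 7735, in total 15,467. The type 1 error for Aim 2 is not stated; two-sided 0.05 is assumed because it reproduces the stated power (0.05/3 would give 64.8%). The share *f* of attenders who met the outcome before their first visit is not in the documents; 5%, 10% and 15% are assumed.

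**Formula.** Power = Φ[(d − 1.96·s0)/s1], where d is the difference, s0 the standard error under the pooled proportion and s1 the unpooled standard error.

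**Step 1: the plan's own figure.** 31.5% v 33.8%, 6400 per group: pooled proportion 0.3265, s0 = 0.008290, s1 = 0.008287. Then (0.023 − 1.96 × 0.008290)/0.008287 = 0.815, and power is 79.2%. The stated 80% reproduces. With actual enrolment at 80% attendance (6185 v 6188) it is 77.9%.

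**Step 2: leave out those already complete.** The set becomes n = 6400(1 − f) per group, with A rate (0.315 − f)/(1 − f). The result depends on what the 2.3 points means.

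- Reading 1: 2.3 points is the effect in all attenders. The planned set keeps 79.2%. The same number of extra screenings in the smaller set is a difference of 2.3/(1 − f) points.
- Reading 2: 2.3 points is the effect in those still due. The planned set then shows only 2.3(1 − f) points, and the restricted set shows 2.3.

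| f (assumed) | n per group | A rate, restricted | Reading 1: planned → restricted | Reading 2: planned → restricted |
|---|---|---|---|---|
| 5% | 6080 | 27.9% | 79.2% → 83.6% | 75.1% → 79.8% |
| 10% | 5760 | 23.9% | 79.2% → 88.5% | 70.5% → 81.3% |
| 15% | 5440 | 19.4% | 79.2% → 93.6% | 65.6% → 84.3% |

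The restricted set has the higher power in every row under both readings.

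**Step 3: all randomised patients.** If the nudge does nothing for the 20% without a visit, the overall effect is 0.8 × 2.3 = 1.84 points. Taking 31.5% as the rate in non-attenders too (31.5% v 33.34%), power is 70.1% at the planned 8000 per group and 68.6% at the actual 7732 v 7735. Like for like, attenders v all randomised is 79.2% v 70.1% at planned numbers and 77.9% v 68.6% at actual numbers. Dropping non-attenders therefore protects power; only the already-screened attenders cost it.

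**Step 4: is the restricted set still a randomised comparison?** The date of the first visit and the screening status before it are both settled before any nudge is given. Assignment to A or B cannot change either through the nudge, so A v B within the set keeps the benefit of randomisation.

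**The case against.** The restriction is openly declared, is the basis of the sample size, and comes with a comparability check and a reweighted analysis. All of that stands. The same argument that validates a still-due set also protects the planned one, since a nudge that starts at a visit cannot influence whether a first visit happens. A reader might infer that selecting on a post-randomisation visit biases A v B. The documents do not support that; the restriction mainly changes the population to which the estimate applies.

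A reader might also infer that the stated 80% power is wrong. It is not: 2.3 points can be read as the detectable difference in all attenders, with dilution already inside it.

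The size of the gain is uncertain. At f = 15%, 0.15/0.315 = 48% of group A completions would precede the first visit, and at 10%, 32%; the upper assumptions may be high. On the FIT route two negative tests are needed and FIT is offered annually, so one early negative test does not settle the outcome.

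The nudge effect in all attenders is a legitimate pragmatic question, and the restricted set answers a narrower one. Nor does not having met the primary outcome equal having an open order: a patient with MT-sDNA or one recent negative FIT may have none, yet would stay in. Finally, this is not the only powered Aim 2 comparison (Black patients have one, at 4.7 points), and the Aim 1 secondary model includes nudge interactions.

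What none of this answers is that the set, as worded, admits patients on whom the nudge cannot act. Reweighting leaves them in.

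**Conclusion.** The point holds as a matter of efficiency and labelling. The Aim 2 set takes in patients whose outcome was settled before any nudge was possible, and it does not match the general intention-to-treat statement. At an assumed 5% to 15% screened before the first visit, excluding them gains about 4 to 14 percentage points of power if 2.3 points is the effect in all attenders, and about 5 to 19 if it is the effect in those still due. Both ranges rest on that assumed share, on two-sided 0.05, and on the planned 6400 per group. The change is worth making because it is cheap and did not lower power in any case examined.

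**What to change.** Define the Aim 2 primary set as patients in arms 2 and 3 with a PCP visit after randomisation who had not met the primary outcome before the first such visit. Call it a modified intention-to-treat set and word the opening of the Analytic plan to allow for it. Keep the reweighted analysis and add beside it an A v B comparison of all 15,467 randomised patients as a supportive intention-to-treat analysis, noting its power of about 69% for 1.84 points.

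The cost is analysis-plan wording. Aim 2 already needs visit data, and section 2.4 describes daily status queries with chart review that track screening. The downside is a somewhat smaller set and an estimate that applies to patients still due at their first visit. Analysis waits until all participants complete 3 years, so the change can be fixed in advance.
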